## Abstract

**Background:**

Integrative medicine (IM) is a patient-centered, healing-oriented clinical paradigm that explicitly includes all appropriate therapeutic approaches whether they originate in conventional or complementary medicine (CM). While there is some evidence for the clinical and cost-effectiveness of IM practice models, the existing evidence base for IM depends largely on studies of individual CM therapies. This may in part be due to the methodological challenges inherent in evaluating a complex intervention (i.e., many interacting components applied flexibly and with tailoring) such as IM.

**Methods/Design:**

This study will use a combination of observational quantitative and qualitative methods to rigorously measure the health and healthcare utilization outcomes of the University of Arizona Integrative Health Center (UAIHC), an IM adult primary care clinic in Phoenix, Arizona. There are four groups of study participants. The primary group consists of clinic patients for whom clinical and cost outcomes will be tracked indicating the impact of the UAIHC clinic (n = 500). In addition to comparing outcomes pre/post clinic enrollment, where possible, these outcomes will be compared to those of two matched control groups, and for some self-report measures, to regional and national data. The second and third study groups consist of clinic patients (n = 180) and clinic personnel (n = 15-20) from whom fidelity data (i.e., data indicating the extent to which the IM practice model was implemented as planned) will be collected. These data will be analyzed to determine the exact nature of the intervention as implemented and to provide covariates to the outcomes analyses as the clinic evolves. The fourth group is made up of patients (n = 8) whose path through the clinic will be studied in detail using qualitative (periodic semi-structured interviews) methods. These data will be used to develop hypotheses regarding how the clinic works.

**Discussion:**

The US health care system needs new models of care that are more patient-centered and empower patients to make positive lifestyle changes. These models have the potential to reduce the burden of chronic disease, lower the cost of healthcare, and offer a sustainable financial paradigm for our nation. This protocol has been designed to test whether the UAIHC can achieve this potential.

**Trial registration:**

Clinical Trials.gov NCT01785485.

## Background

This article describes the protocol for a two-year study of the health and economic impact of a primary care integrative medicine (IM) clinic. IM is defined as a health promoting, prevention-oriented clinical paradigm that explicitly includes conventional medical treatment together with the use of complementary medicine (CM) modalities that have sufficient evidence and safety for use [1-5]. Practice models in IM are emerging [6], but most of the models provide consultative or specialty care; few provide primary care. There are also few methodologically valid health services research studies on the clinical and cost effectiveness of IM practice models, particularly for primary care [7-12].

The evaluation of a IM primary care model presents a number of methodological challenges. Some are the result of the evolving nature of the concept of IM [12], and most have been discussed in the literature to illustrate the complex needs of CM research [13-20]. In general, these challenges apply to research involving any complex intervention (e.g., a new care delivery model) [21-24]. Each challenge is discussed below accompanied by recommended solutions.

### Complex, individualized intervention

Although IM is defined as both a clinical treatment paradigm and a practice organization model, the existing evidence base for IM depends largely on studies of the individual components [7,8,10,14,25]. While IM combines conventional and evidence-based CM modalities (having practitioners who can offer these CM modalities is an important aspect of the practice organization model), it is also a larger clinical paradigm for a process of whole person, patient-centered, healthcare that embraces the innate healing capacity of the human organism and attends to the importance of lifestyle [2,26,27]. Whether seen as a clinical paradigm or as a practice model, IM meets the definition of a complex intervention. It consists of a number of interacting components that make up and affect care, and these components are applied with a large degree of flexibility and tailoring [28]. To create an evidence base for IM itself, studies that characterize and evaluate the outcome of intact IM clinic practices are needed.

Several researchers have recommended that complex interventions simply be studied as "black boxes” [14,16,19,20]; as interventions whose outputs can be measured, but whose internal mechanisms are unknown. Since subjects can be randomized to one black box or another, no new methods are required. Others recommend that the boxes be "unpacked”—that every element in the intervention be defined and its outcomes measured [29,30]. The "black box" approach offers no assurance that the box contents are a valid representation of the intervention; however, given the number of different treatments and potential diagnoses, complete "unpacking" may prove an insurmountable measurement, analysis, and interpretation challenge. The concept of implementation fidelity offers a balance between these two extremes. Outcomes are still measured for, and attributed to, the intervention as a whole (the “box”). However, the contents of the box are defined and measured to document what was actually delivered—i.e., what the box contains.

When a study compares two drugs (or a drug to placebo), all else is held (or assumed to be) equal – in part through randomization, and in part through strict study protocols, including participant and practitioner blinding. As both comparison groups are being treated within the same practice model (e.g., conventional primary care), little, if any, effort is given to defining that model. Faithfulness to the intended intervention, defined as Intervention implementation fidelity, is ensured through monitoring adherence to protocols. The objective is to ensure that the only difference between groups is receipt of the drug under study [22].

In contrast, when two practice models are compared in a study, very little can be held equal. The study protocol is by necessity less prescriptive as to what is delivered, when, how, and by whom. The constraints placed upon possible interventions are loosened to allow practitioner autonomy in individualizing patient care. Not only may different treatments be offered, but different practitioners with different training may diagnose and then prescribe those treatments with different clinical goals and under different philosophies of care. Some method of defining the practice models is needed to capture and measure differences to ensure that interventions are implemented as intended, and to know what is actually being compared.

The concept of intervention implementation fidelity emerged in the 1960s in the field of psychotherapy when early attempts to sort out design and interpretive problems in outcomes studies proved impossible. For an overview of fidelity and its measurement, see Bond et al. [31]. Since the 1960s, including measures of intervention fidelity has become a standard requirement for research in a number of applied fields, including medicine [21,22,24,28,32,33]. Fidelity monitoring is important for the interpretation of study results (e.g., avoidance of Type III error – erroneously concluding that an intervention had no impact when it was actually not implemented), and for replication [22,23,32]. Fidelity measures can also be used as covariates in the analyses to determine treatment effect and avoid invalid statistical conclusions [24].

Assessment of implementation fidelity will help with defining ‘what was measured’ in complex interventions. However, to understand the ‘why it happened’ causal effects of IM, a number of researchers have recommended the use of mixed methods—e.g., including qualitative methods in the study design [13,15,20,21,34]. Randomized controlled trials (RCTs), even when coupled with advanced quantitative methods, cannot explain complex causal relationships [20,21]. Well-designed multi-method studies allow a deeper understanding of the mechanisms that might be at work in the intervention [21].

### Whole person outcomes as markers of effectiveness

IM’s focus on treating the whole person, is believed to have outcomes beyond those associated with treatment of the targeted condition [25,35]. The emphasis on self-care, the benefits of a good patient-practitioner relationship, and the promotion of the body’s self-healing capacity are all believed to result in enhanced health [35]. In parallel to the concept of treating the whole person is the concept of using a whole system of healthcare services delivery. In IM this includes a focus on the patient-provider relationship and a full range of potential treatments. Together these result in the need to measure outcomes across a number of dimensions (e.g., spiritual, social, physical, mental, emotional) [29,36]. The Federal Coordinating Council for Comparative Effectiveness Research (CER) has stressed the importance of “*assessing a comprehensive array of health-related outcomes…”*[37] to provide the information that patients, clinicians and policy makers need to make good healthcare decisions.

### Patient preferences and the infeasibility of randomization

Patients are rarely neutral about IM. They typically indicate strong preferences for or against this approach to healthcare, which makes it hard to accrue patients in randomized trials [14]. In the absence of the ability to randomize appropriately, observational approaches are recommended [16,18]. Observational studies are also recommended for complex systems [19] and to capture actual practice [29]. When well-designed, they have been found to produce results comparable to RCTs, neither over- nor underestimating treatment effects [38-40]. CER methods allow for studies of all types of health-related interventions, including delivery systems [21], and recognize observational studies as valid designs [41-43].

The protocol described in this article addresses the clinical and economic evaluation of an IM primary care clinic. Although the outcomes and processes of care of this particular clinic, as defined in its business plan, are being evaluated, it is anticipated the findings from this study will contribute to IM health services research in general. Because IM practice is a complex intervention, the study design includes fidelity monitoring and evaluation, and an observational design that includes qualitative data collection and analysis. And because IM practice offers whole-person care, a broad range of outcomes are being measured.

## Methods/Design

This two-year study is Phase II of a two-phase, three-year project. The purpose of Phase I was to design the protocol for the Phase II study, including clarifying the design of the IM clinic model to be tested and identifying the measures to use for outcomes and to monitor treatment fidelity. The purpose of Phase II is to conduct a prospective outcomes evaluation of the clinical and cost effectiveness of an IM professional practice model for adult primary care.

### Study design

A combination of observational quantitative and qualitative study designs will be used to measure the health and healthcare utilization outcomes of a primary care IM clinical model. Where possible, the clinical and economic impacts seen in this IM model will be compared to data available from one or more comparison groups (see discussion of comparison groups below). When comparison group data are not available for outcomes —e.g., for most of the self-report data and for the medical records data—baseline values for clinic participants will be compared to those measured during and after treatment. Table 1 shows the types of comparisons planned for each outcome data category for the observational study.

**Table 1 T1:** Outcomes measured for the UAIHC

	**Frequency of measurement**	**Pre/post comparisons**	**Comparisons against control group(s)**
Healthcare utilization and costs	One year prior and one year post-study enrollment	X	X^*^
Diet quality	BL, 3, 6, and 12 months	X	X^**^
Exercise	BL, 3, 6, and 12 months	X	X^**^
Patient satisfaction	3, 6, and 12 months	X	X^***^
Self-report health outcomes	BL, 3, 6, and 12 months	X	
• Self-efficacy			
• Stress			
• Sleep quality			
• Pain			
• Fatigue			
• Depression			
• Anxiety			
• Health-related quality of life			
• Well being			
• Work productivity			
• Condition-specific			
• outcomes			
Medical records data	3, 6, and 12 months	X	

BL = baseline (clinic enrollment).

^*^Primary outcome; comparison is to two matched control groups.

^**^Comparison here is to national (and where available statewide) averages from the Center for Disease Control and Prevention’s Behavioral Risk Factor Surveillance System (BRFSS) survey [51].

^***^Comparison here is to national and regional norms using the Consumer Assessment of Healthcare Providers and Systems (CAHPS) Adult Visit Survey 2.0 data [50].

Because the IM professional practice model is a complex intervention, implementation fidelity will be assessed, in addition to clinical and economic outcomes. Fidelity data (gathered on patients’ and practitioners’ experiences and from medical record data) will serve four purposes. First, these data will be used as a measure of intervention integrity—i.e., was the intervention/practice delivered as intended. Second, because integrative primary care has not previously been defined and evaluated, and since the clinic under study is new, and thus continuously developing and modifying operational and treatment protocols and procedures, these fidelity data will also describe what happened. Third, data on operations and how they may have evolved over time are important as potential covariates in the analysis of outcomes, for proper interpretation of results, and for external validity and replication. Finally, fidelity data provide quality control feedback to clinic staff as to how the IM clinic model is being implemented by staff and perceived by patients. This will allow for quality improvements of the IM primary care clinic over time.

This study received the approval of the University of Arizona Institutional Review Board, and is registered in clinicaltrials.gov (NCT01785485).

### Setting and Participants

Data used in the evaluation will be gathered from eligible and consenting participants who are also patients enrolled at the University of Arizona Integrative Health Center (UAIHC), an integrative medicine adult primary care clinic in Phoenix, Arizona. Operated in conjunction with District Medical Group, Inc., UAIHC is financed through insurance reimbursements and a patient membership fee structure. At present, two major employers in the Phoenix area pay a portion of the membership fee for their employees who elect UAIHC as their primary care provider. There are four groups of study participants. The first (and main) group consists of eligible participants from the clinic patient population for whom clinical and cost outcomes will be tracked indicating the impact of the UAIHC clinic (n = 500). The second and third groups consist of clinic patients (n = 180) and clinic personnel (n = 15-20) from whom fidelity data will be collected. The fourth group is made up of the patients (n = 8) whose path through the clinic will be studied in detail using qualitative methods. The clinic patients involved in the outcomes study sample may or may not be included in the fidelity patient sample, and vice versa. However, the qualitative data sample is expected to be a subset of the outcomes sample.

### Outcomes sample

Only patients who are members at UAIHC and who meet the inclusion/exclusion criteria are eligible to enroll in this study. Participation in the study will continue for at least one year after enrollment. It is anticipated that at least 500 patients will consent to participation during the first nine months of the study. Our primary outcome for our main analysis is change in total costs (see the Analysis section below). Using the standard deviation seen in a set of healthcare utilization data from a related group, a sample size of 200 patients should be sufficient to detect a small effect size (Cohen’s d = .20) difference in total costs at a .80 power using an alpha of .05. Therefore, our expected sample size of 500 may also allow for some subgroup analysis. Inclusion criteria: 1) Enrollment in primary care (members) at UAIHC; and, 2) adults ages 18 or older. Exclusion criteria: 1) currently pregnant at time of recruitment; 2) patients who attend the UAIHC clinic as “consultation-only” patients; and, 3) significant cognitive impairment to the extent that the individual is unable to understand the consent and respond to questionnaires.

All new patients will be advised by their primary care physician that they may be eligible to participate in a study to evaluate the effectiveness of the UAHIC. Prior to checkout, patients have an exit session with the University of Arizona (UA) Study Coordinator. During this session (or if necessary, through a follow-up phone call), the Study Coordinator will explain the nature of the study and make a determination of study eligibility, and if appropriate, consent the patient. Patients who joined the UAIHC before study start (July 2013) will also have the opportunity to participate. The study will be explained at their first UAIHC visit after study start.

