The fifth analysis will focus on the subset of patients for which health insurance claims data are available and will utilize a matched comparison design. Prior to analysis all claims data for each individual (treatment and comparison groups) will be aggregated (by summation) into per health plan member per month (PMPM) totals of paid amounts (the amount paid by the health plan to the practitioner) for each of the following cost categories: total, inpatient, outpatient, emergency room, physician, and pharmaceutical claims. Similarly, the numbers of outpatient visits, hospital stays and emergency department visits will also be aggregated for each individual. The primary outcome will be total cost. Two comparison groups from de-identified claims data will be created—one using simple matching (e.g., by age and gender) and one using propensity scores [49]. After the comparison groups have been selected, simple descriptive analyses will show average PMPM costs and healthcare utilization (including standard deviations and other measures of dispersion) pre- and post- enrollment (or an equivalent date for the comparison groups) by gender, age, baseline diagnosis and by treatment and comparison group. Because cost data tends to be highly skewed, average PMPM costs and healthcare utilization pre/post enrollment, and the change in costs and utilization pre/post between the treatment and each of the comparison groups will be reported as mean differences with confidence intervals calculated using bootstrap methods [83,84]. Because of the number of data points for each patient (e.g., up to 12 PMPM values pre-enrollment and 12 post-enrollment), HLM [80-82] will be used to estimate the pattern of change in healthcare utilization and costs over time, and to explore the determinants of those patterns. Fidelity measures with significant changes over time [24], demographics, participants’ membership level and baseline diagnoses will be included as covariates in these models. Finally, changes in costs between groups will be compared to changes in patients’ CVD risk.

Results for the last two analyses will be reported following the Strengthening the Reporting of Observational Studies in Epidemiology (STROBE) guidelines [85]. For all outcomes, the estimated treatment effects will be reported using their original outcome scale and including confidence intervals.

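### The 200 patients stated for 80% power fit a one-group or paired test, whereas the primary cost outcome is a between-group comparison in a claims subset of unstated size

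*Protocol article*

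**What the plan says.** **Power statement (Methods/Design, Outcomes sample).** The quantity powered is named: "Our primary outcome for our main analysis is change in total costs", with a pointer to the Analysis section. The SD comes from an outside source that is not shown: "Using the standard deviation seen in a set of healthcare utilization data from a related group". On that basis the article concludes that "a sample size of 200 patients should be sufficient to detect a small effect size". The numbers attached to this conclusion read "d = .20) difference in total costs at a .80 power using an alpha of .05". The next sentence draws an inference: "Therefore, our expected sample size of 500 may also allow for some subgroup analysis". The text does not name the test or its sidedness. It does not say whether 200 is a total, a number per group or the clinic patients alone, or whether the SD is that of cost or of change in cost.

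**Comparison (Study design, Table 1).** Utilization and costs are ticked both for pre/post and for control-group comparison. The footnote on the control-group tick reads: "Primary outcome; comparison is to two matched control groups".

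**Cost analysis (Analysis, fifth analysis).** "The fifth analysis will focus on the subset of patients for which health insurance claims data are available and will utilize a matched comparison design". Total cost is its primary outcome. It reports pre/post costs and also the difference in pre/post change between clinic patients and each comparison group, as mean differences with bootstrap intervals.

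**Data source (Comparison group(s); Health Insurance Claims Data).** Claims come only from patients whose employers grant access. Controls are drawn from the rest of the same claims file. Neither the number of participants with claims nor the matching ratio is given.

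**The concern.** The power statement and the analysis it points to appear to describe different contrasts. A pre/post change in one group carries the variance of that group only. A difference in change between clinic patients and controls also carries the controls' variance, which at 1:1 with independent groups doubles the variance and so doubles the number needed per group.

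The denominator is a second problem. The 500 are the whole outcomes sample, but cost is analysed only in those with claims. Comparing 200 with 500 therefore does not show a margin for cost.

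This is the article's only power statement for its primary outcome. If it does not apply to the primary comparison, the investigators would begin with a mistaken view of the precision to expect, and would have no prompt to choose a matching ratio that makes good use of the available controls.

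**Working it through.** **Inputs.** From Outcomes sample: n = 200, d = 0.20, power 0.80, alpha 0.05. Assumed because not stated: two-sided test (z = 1.960, and 0.842 for 80% power), and d scaled to the SD of cost change. The SD itself then cancels. Results use the normal approximation, with the t-test value in brackets where it was computed.

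**1. Reproducing the stated figure.** One group or paired:

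n = ((1.960 + 0.842) / 0.20)² = 196.2, so 197 (t: 199).

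Power at 200 = Φ(0.20·√200 − 1.960) = Φ(0.868) = 0.807 (t: 0.804).

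This reproduces the 200. Other standard versions do not: one-group one-sided needs 155, two groups 1:1 one-sided need 310 per group, and two groups 1:1 two-sided need 393 per group.

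**2. The between-group contrast, independent groups, 1:1.**

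n per group = 2 × 196.2 = 392.4, so 393 (t: 394).

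Power with 200 per group = Φ(0.20·√(200/2) − 1.960) = Φ(0.040) = 0.516 (t: 0.514). One-sided it is 0.64. If 200 were the total (100 per group), two-sided power would be 0.29.

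**3. More controls per participant.** With 200 participants and k independent controls each, power = Φ(0.20·√(200/(1 + 1/k)) − 1.960):

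| k | Power with 200 | Participants needed for 80% |
|---|---|---|
| 1 | 51.6% | 393 |
| 2 | 63.7% | 295 |
| 5 | 73.3% | 236 |
| 10 | 76.9% | 216 |
| 20 | 78.8% | 207 |
| 50 | 80.0% | 201 |

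**4. Correlation within matched pairs.** For 200 pairs with correlation r in cost change, the pair difference has variance 2(1 − r) relative to one group: r = 0 gives 51.6%, 0.2 gives 60.9%, 0.3 gives 66.7%, and 0.5 gives 80.7%.

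Ratio and correlation combine. With 4 controls and r = 0.2 between all members of a set, the relative variance is 1 + (1 + 3 × 0.2)/4 − 2 × 0.2 = 1.0. That equals the one-group case, so power is again about 81%.

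**5. Number with claims.** Power at 1:1, independent groups, over an assumed range because the article gives no number:

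| With claims | Share of 500 | Power |
|---|---|---|
| 100 | 20% | 29% |
| 200 | 40% | 52% |
| 300 | 60% | 69% |
| 400 | 80% | 81% |
| 500 | 100% | 89% |

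**6. Which SD.** If d were instead scaled to the SD of cost at one time, with pre/post correlation ρ, the SD of change is √(2(1 − ρ)) times that SD. With 200 per group, power is 29% at ρ = 0, 39% at 0.3, 52% at 0.5 and 73% at 0.7.

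**The case against.** The strongest defence is that 200 does power something the article plans. Table 1 ticks pre/post for cost, and the fifth analysis reports pre/post cost changes. The same formula is also correct for matched pairs if d is scaled to the SD of the pair difference, and the article does not say which SD was used. This stands. A reader might infer that the figure is valid solely for a one-group test, but the documents do not support that, as step 4 shows.

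A reader might also infer that the planned comparison has 51% power. That is not supported either. It needs 200 participants with claims, 1:1 matching, independent groups and a two-sided test, and the article fixes none of these. Controls come from the remainder of the claims file, so several per participant are open. The HLM with covariates may add precision that these figures ignore. The reported confidence intervals would also reveal imprecision, so it does not follow that a null cost result must be misread.

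The subgroup sentence is hedged and does not mention cost. The fourth analysis plans condition-specific results in the all-patient cohort, where 500 is the right denominator, and the Discussion concedes that enrollment may fall short and that usable claims data are hard to obtain.

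The main criticism remains. The power sentence is tied to the primary outcome, and Table 1 attaches that label to the comparison with control groups. The conditions that would rescue 200 are demanding. Correlation induced by matching cannot exceed the share of variance in cost change that the matching variables explain. One of the two algorithms uses age and gender, which would have to explain about half. Nothing in the article suggests that they do.

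Finally, since no SD is given, the document offers no basis for judging how large d = 0.20 is in money.

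**Conclusion.** The point holds in conditional form. The stated 200 matches a one-group or paired calculation and is not shown to give 80% power for the between-group difference in cost change.

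Under independent groups and a two-sided test, 200 participants give about 51% at 1:1 and 77% at 10:1, and 1:1 needs 393 to 394 per group for 80%. The stated 80% is reached with 200 only if something unstated applies: a within-pair correlation near 0.5, about 50 controls each, or a mix such as 4:1 with correlation 0.2.

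Separately, and whatever the test, 500 is not the sample size of the cost analysis. Across an assumed 100 to 400 participants with claims, power at 1:1 runs from 29% to 81%. So 500 is not shown to be a surplus for cost, although it may serve subgroup work on the all-patient outcomes.

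The arithmetic is certain. The actual power of the study cannot be determined from the article. The statement should be corrected because it is the only one supporting the primary outcome and the correction is cheap.

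**What to change.** - Restate the power for the between-group difference in cost change, based on the expected number of participants with claims. Name the test, the matching ratio, the sidedness, the SD to which d refers, and any assumed within-set correlation with its basis. If 200 was meant for the pre/post comparison, say so and give the between-group figure beside it.
- Match several comparison members per participant from the remainder of the claims file. Most of the gain comes early: with 200 participants, power goes from 51% at 1:1 to 64% at 2:1, 73% at 5:1 and 77% at 10:1.
- Limit the inference from 500 to subgroups to the all-patient cohort outcomes, and do not extend it to cost.

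The cost is some rewording and one matching setting. No additional patients are needed. The downsides are a less favourable stated power and somewhat looser matches at higher ratios.
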